For participants in the intervention arm, sample 2 is tested with the FilmArray Pneumonia Panel in the ICU as soon as possible (in all cases within 24 h). The results are reviewed, as soon as they are available, by the treating clinician, whose antibiotic prescription is directed by the trial-specific algorithm and local prescribing guidelines. It is anticipated that the great majority of intervention participants will receive either only one dose of empirical treatment or perhaps none before the FilmArray test result allows treatment to be targeted. The participant will continue receiving normal clinical care. For participants in the control arm, sample 2 is frozen within 24 h, and the FilmArray test is run by either of the two central laboratories located at the University College London and University of East Anglia, without the result being made known to the treating clinicians. Where consent is given, the spare sample may be retained for future use in ancillary studies.

Future specimens from the same intervention group participant may be tested using the FilmArray test provided the following conditions are met: (i) the participant has not withdrawn from the trial; (ii) the specimen is taken as part of the routine care, and a matching specimen (sample 1) is sent to the microbiology laboratory; (iii) testing is no less than 72 h after the previous specimen and would have been taken regardless of the trial; (iv) there is enough specimen for the machine testing; and (v) the participant was randomised to the trial ≤ 21 days previously.

As the intervention happens immediately after randomisation, no special strategies to improve adherence are specified in the trial. All standard care options are available to clinicians at all times. Barriers to algorithm adherence are explored and analysed as part of the behavioural study. Therefore, there are no special criteria for discontinuing or modifying the allocated interventions.

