### Sample size

The trial aims to recruit 552 patients over a 24-month recruitment period. Calculation of the required sample size is based on the co-primary outcomes of clinical cure at 14 days and antimicrobial stewardship at 24 h. The trial will investigate non-inferiority in terms of clinical cure and superiority for antimicrobial stewardship. Calculations aim to achieve 90% power and 5% significance for the co-primary analyses and allow for up to 5% attrition. Data for the first 100 patients from work package 2 provide estimates for the sample size calculation. For the non-inferiority outcome, a clinical cure rate of 55% is assumed in both trial arms, and the non-inferiority limit is defined to be 13% [23–27]. Under standard care, it was estimated that 53% of patients received antibiotics that were both appropriate and proportionate within 24 h of clinical diagnosis, and it is clinically important to improve this by at least 20% (to 73%). The planned sample size of 552 patients will provide 91% power for the non-inferiority outcome analysis and 99% power for the superiority outcome, resulting in 90% for the co-primary analysis (0.91 × 0.99 = 0.9), under the conservative assumption of no correlation between the outcomes [28]. The sample size is not inflated for non-compliance, as none is expected.

The estimates used for both cure rate and antimicrobial stewardship are consistent with those reported in published studies [24–30].

The trial originally aimed to recruit 466 participants, but this was updated to 552 to reflect an expected lower estimated cure rate for pneumonia among COVID-19 patients (postulated at the time to be between 20 and 40% vs. an original estimate, pre-COVID, of 70%). Assuming a maximum of 30% of the final sample might be COVID-19 patients, the minimum expected overall cure rate is 55%, as used in the new sample size calculation. Estimates were based on the data already collected and decided in consultation with the principal investigators.

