### Analysis

The co-primary outcomes will be summarised as the proportion of participants where:
Clinical cure was achieved by 14 days after randomisation;Active and proportionate antimicrobial therapy has been initiated within 24 h of randomisation.

For both outcomes, the effect of the intervention will be described using a difference in proportions, and an odds ratio, each calculated with a 95% confidence interval. For the non-inferiority analysis of clinical cure, confidence intervals will be one-sided. Estimates will be obtained from regression models that allow for study site. Similar approaches will be used for binary secondary outcomes. For continuous secondary outcomes, the groups will be compared using standard regression models (where normality assumptions are satisfied) to obtain the differences in the means allowing for site and adjusting for baseline values where these are available.

In all superiority analyses, participants will be analysed on an intention-to-treat basis, regardless of clinicians’ decisions in using the FilmArray test results and the associated algorithm, or in respect of the antibiotics prescribed. A Microbiology Committee, comprising three independent members and one member of the study team, has been set up to review the prescribing decisions. The committee assesses whether prescribing is active and proportionate at 24 h and 72 h post-randomisation for each patient and is blinded to the study arm. Per-protocol analysis will provide the primary results for the non-inferiority outcome. The committee Terms of Reference are shown [see Additional File 4].

Data analysts will not be blinded. A detailed statistical analysis plan will be finalised before analysis and will include details of any relevant sub-group or adjusted analyses. It will be made available, upon request, from the Trial Management Group.

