## Discussion

ICUs have greater per patient antibiotic use, and so exert more selection pressures for resistance, than elsewhere in hospitals, with some (albeit mixed) evidence of correspondingly higher resistance rates [3]. Sub-optimal treatment leads to poorer outcomes for patients, including side effects from over-treatment and increased mortality from under-treatment of severe and resistant infections. The cost to society is also high, both in human terms and in respect of the cost of hospital stays.

Current microbiology techniques to identify pathogens and their resistance are slow and outdated and do not always grow a pathogen despite clinical evidence of infection. There are few new antibiotics reaching the market, and recently licensed ones do not wholly overcome resistance; moreover, they are vulnerable to new modes of resistance. The UK government’s ‘Contained and Controlled, 20-year vision for antimicrobial resistance’ [36] confirms the vital need to find alternative, evidence-based models for antibiotic use.

Molecular diagnostics, such as the FilmArray Pneumonia Panel, offer the potential to achieve this goal by rapidly and simultaneously identifying organisms and critical resistance genes directly from the clinical specimen, without culture. The partner algorithm being trialled together with the FilmArray Panel offers the potential to identify a proportionate antibiotic choice for each identified pathogen and resistance genotype detected—if clinicians are willing to adopt this approach in challenging and severely ill ICU patients. If successful, this work could be extended to other clinical settings, though the cost advantage, which will be analysed, is likely to be greatest in ICUs.

In addition, this trial will, to our knowledge, be the first to explore the human factors that interpose between a rapid microbiological result and the clinicians’ contingent actions that follow (or not). It has been designed to capture both the extent of clinicians’ compliance with the result-driven recommendations, and the reasons underlying such compliance, or lack of it.

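### Non-inferiority in clinical cure rests on a per-protocol result with no stated intention-to-treat counterpart, in an open-label trial where prescribers may set the test aside

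*Protocol article*

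**What the plan says.** The Analysis section of the protocol article names the population for each co-primary outcome. For stewardship: "In all superiority analyses, participants will be analysed on an intention-to-treat basis". The rest of that sentence makes plain that what prescribers did with the test, the algorithm and their choice of drug has no bearing on inclusion. For cure: "Per-protocol analysis will provide the primary results for the non-inferiority outcome". No section requires an intention-to-treat analysis of cure, or agreement between the two populations. Under Primary objectives, the trial succeeds only if both co-primary outcomes are met, so the cure result is decisive.

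The per-protocol population is not defined in the article. The Analysis section says "A detailed statistical analysis plan will be finalised before analysis and will include details of any relevant sub-group or adjusted analyses"; that plan is not at hand.

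Four other places bear on the point:
- **Design:** the trial is open-label once a participant is randomised.
- **Intervention:** no measures to improve adherence are specified, and "All standard care options are available to clinicians at all times".
- **Sample size:** no inflation for non-compliance, because none is expected.
- **Behavioural evaluation:** assuming complete compliance with the test's recommendations is described as neither appropriate nor realistic.

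**The concern.** The trial compares two strategies. One is a rapid result plus an algorithm, used by clinicians who keep full discretion; the other is local standard care. A per-protocol set conditions on what happens after randomisation. If it conditions on whether the clinician followed the result or algorithm, only the intervention arm has such guidance to depart from. A selected part of that arm would then be compared with nearly all of the control arm. If the reasons for departing relate to prognosis, the difference in cure mixes the effect of the strategy with that selection.

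Cure is the safety side of the trial: failure includes pneumonia-related death, septic shock and relapse. A false finding of non-inferiority could support a strategy that cures fewer patients, and a bias in the other direction could reject a sound one. As written, no randomised comparison of cure is required to confirm the verdict.

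**Working it through.** **Inputs from the article.** Cure 55% in both arms, margin 13 points, 552 patients, 1:1 allocation, 91% power for non-inferiority (Sample size; Design). "Calculations aim to achieve 90% power and 5% significance for the co-primary analyses and allow for up to 5% attrition" "For the non-inferiority analysis of clinical cure, confidence intervals will be one-sided"

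**Assumed, because the article gives neither.** The share f of the intervention arm excluded (10%, 20%, 30%), and the cure gap g between retained and excluded patients. Exclusions are taken from the intervention arm only.

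**Formula.** SE = √[pC(1−pC)/nC + pT(1−pT)/nT]; P(non-inferiority declared) = Φ[(0.13 − (pC − pT))/SE − 1.645].

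**1. The plan's own figure.** n per arm = (1.645 + 1.341)² × 2 × 0.55 × 0.45 / 0.13² ≈ 261.1, so 262. Then 524/0.95 = 551.6, so 552. With 262 per arm SE = 0.0435 and power = Φ(0.13/0.0435 − 1.645) = 91.1%. The stated figure reproduces at one-sided 5% (one-sided 2.5% would give 85%). It allows for attrition but for no exclusion due to non-adherence.

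**2. False non-inferiority under per-protocol.** The true intention-to-treat difference is set at the margin (55% v 42%), with nC = 262 and nT = 262(1−f).

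(a) *Observed gap.* Excluded intervention patients cure g points less often than retained ones, so retained cure = 0.42 + f·g. For f = 20%, g = 25 points: 0.42 + 0.05 = 0.47; difference −0.08; SE = 0.0462; Φ(0.05/0.0462 − 1.645) = 28.7%.

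(b) *Prognostic gap, excluded patients get the control outcome.* The whole deficit then falls on retained patients, so retained cure = 0.55 + f·g − 0.13/(1−f). For f = 20%, g = 25 points: 0.55 + 0.05 − 0.1625 = 0.4375; difference −0.1125; SE = 0.0460; Φ(0.0175/0.0460 − 1.645) = 10.3%.

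(c) *Excluded patients fare better.* Retained cure = 0.42 − f·g.

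| Scenario | f = 10% | f = 20% | f = 30% |
|---|---|---|---|
| No gap | 5.0% | 5.0% | 5.0% |
| (a) observed gap, 25 points | 14% | 29% | 47% |
| (b) prognostic gap, 25 points | 8.0% | 10.3% | 10.7% |
| (b) prognostic gap, 15 points | 5.1% | 4.5% | 3.1% |
| (c) excluded 20 points better | 1.8% | 0.6% | 0.2% |

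**3. Intention-to-treat alone.** Suppose the deficit under full adherence is 13 points and non-adherent patients get the control outcome. The intention-to-treat deficit is then 0.13(1−f). Tested with 262 per arm, non-inferiority is declared in 8.9%, 14.8% and 22.7% of trials at f = 10%, 20% and 30%.

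**4. Power when cure is truly equal and there is no gap.**

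| Rule | f = 10% | f = 20% | f = 30% |
|---|---|---|---|
| Per-protocol alone | 89.7% | 88.0% | 85.8% |
| Both populations required | about 89% | about 87% | about 84% |

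The loss against 91% comes mostly from smaller numbers; requiring both populations takes about one further point. Multiplying by the article's 99% for stewardship gives joint power of roughly 88%, 86% and 83% under the both-populations rule, against the stated 90%. If the same shares were excluded from both arms, per-protocol power alone would be 88%, 85% and 80%.

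**The case against.** Per-protocol is a recognised population for non-inferiority, because intention-to-treat can hide a real deficit; step 3 shows this is not a small matter here. The wording of the primary objective, which concerns patients treated according to the test and algorithm, also gives per-protocol a legitimate place. And naming it as the source of the primary result does not rule out a supporting intention-to-treat analysis. All of this stands. It supports using both populations, not giving per-protocol the sole stated say.

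A reader might go further and infer that per-protocol removes patients from one arm only, by prescriber judgement, and so manufactures non-inferiority. The article does not support that:
- **Definition.** The set is undefined here, and its definition may properly sit in the analysis plan. The sentence on what intention-to-treat disregards suggests adherence-based exclusion but does not state it. Since the Intervention section permits all standard options, an override need not count as a deviation.
- **One arm only.** Eligibility, the specimen window and the handling of the second sample apply in both arms and could also define the set.
- **Direction.** The Discussion makes the benefit conditional: "if clinicians are willing to adopt this approach in challenging and severely ill ICU patients". That describes the ICU population; it does not say that overrides cluster in the sickest. The Background points the other way when it describes clinicians reluctant to change treatment in patients who are doing well, though it says so of culture results.
- **Size.** The 14% to 47% range assumes that excluded patients share the full deficit. If they receive the control outcome, the same 25-point gap, taken as prognostic, gives 8% to 11%.
- **Unblinded analysts.** The article says that analysts are not blinded. It does not say that they will decide per-protocol membership.

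**Conclusion.** The concern holds in a limited form. The article fixes a deciding analysis for cure that may condition on post-randomisation prescribing, and it states no intention-to-treat counterpart. In an open-label strategy trial with free prescribing and expected departures, that leaves the safety co-primary open to a bias of unknown direction. Against a nominal 5%, false non-inferiority with 10% to 30% excluded could be below 5%, about 8% to 11%, or 14% to 47%. Which of these applies depends on the per-protocol definition, the excluded share and the prognosis of those excluded, none of which the article gives. If exclusion is unrelated to cure, the error stays at 5% and only power is lost.

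One part needs no such assumption. Sample size expects no non-compliance, while Behavioural evaluation treats full compliance as unrealistic. The 91% power holds only if nobody is excluded for non-adherence.

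**What to change.** 1. Replace the per-protocol sentence in Analysis with a rule such as: non-inferiority in clinical cure will be concluded only if the lower bound of the one-sided 95% confidence interval for the difference (FilmArray minus standard care) lies above −13 percentage points in both the intention-to-treat and the per-protocol populations. The intention-to-treat condition holds false non-inferiority for the randomised comparison at about 5% whatever the exclusions; the per-protocol condition guards against dilution.
2. State that per-protocol membership will be fixed without sight of cure data.
3. Reconcile Sample size with Behavioural evaluation on expected compliance, and note that the 91% power assumes no exclusion for non-adherence.

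**Cost.** A few sentences and one further run of the same model. The success rule becomes slightly stricter: non-inferiority power is about 84% to 89% if 10% to 30% of the intervention arm is excluded and there is no cure gap. If the sponsor wished to restore 91% for the per-protocol analysis alone under those exclusions, the total would rise from 552 to about 582, 619 or 670; the both-populations rule would need slightly more.

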### Health economics evaluation

To determine whether the trial outcomes justify costs, a cost-effectiveness study will be conducted from a hospital perspective. The outcome measure used will be the same as the main study co-primary outcome. If the two arms of the study are found to be equivalent in terms of clinical cure of pneumonia at 14 days post-randomisation, a cost-effectiveness analysis will be undertaken to evaluate the incremental cost per additional patient receiving active and proportionate antibiotics within 24 h of clinical decision to prescribe antibiotics for HAP/VAP. If equivalence in clinical cure is not established but there is an improvement in antibiotic stewardship, interpretation will be more difficult—a decision-tree model will be used to explore the implications.

The EuroQol EQ-5D-5L, a generic health-related quality-of-life measure [31], will be sought from patients at 21 days to inform the economic evaluation and economic model, but will not be suitable for estimating quality-adjusted life-years (QALYs) for all trial participants. This is because only the most-recovered subset of participants will be well enough to complete the EQ-5D-5L at 21 days, meaning that results will not be representative of the whole INHALE sample.

Data collection for resource use will be limited to the patients’ hospital stay, meaning that an ‘NHS and personal social services perspective’, as recommended by NICE [32], will not be possible. Costs will be estimated solely from the perspective of the hospital.

Estimates of costs and effects will be used to calculate the incremental cost-effectiveness ratios (ICERs), evaluating the incremental cost per additional patient receiving active and proportionate antibiotics within 24 h of the decision to prescribe antibiotics for HAP/VAP. Where appropriate, regression-based methods will be used to allow for differences in baseline characteristics. Uncertainty in data will be accommodated by the use of cost-effectiveness acceptability curves (CEACs), which estimate the probability that the intervention is cost-effective at different monetary valuations of the outcome measure. As costs will be estimated from routinely collected hospital data, we would not expect high rates of missing data. This approach constitutes a ‘within-trial’ economic analysis, conducted during the clinical trial, and will constitute the primary economic analysis.

As the study population will be highly heterogeneous in respect of underlying illness or trauma precipitating ICU admission, economic evaluation may not be straightforward. Additionally, the trial will take place within a short timeframe, so long-run outcomes will not be available. Rather, to explore the effect of assumptions and potential variability, a decision-tree model will be further developed across the entire INHALE programme. Data from the literature will be used to estimate the potential long-run health-related quality of life (HRQoL) effects of HAP/VAP, as well as estimating a cost/QALY approach. Assumptions as to the health benefits of different pathways and outcomes will allow an exploration of potential longer-term effects (e.g. potential effects on antibiotic use, resistance and related health outcomes). Literature data [33] and clinical opinion will be incorporated where necessary. This decision-tree model will be used to explore a range of ‘what if’ scenarios, evaluating different consequences of results from the trial. Assumptions about the consequences of care provided and of improved antimicrobial stewardship will be formulated. This approach is speculative but will potentially inform decision-makers as to the potential consequences of rapid microbiological diagnostics. The results of this model will constitute a secondary analysis. Details of the proposed methods for the within-trial analysis and the economic model will be pre-specified in a health economics analysis plan (HEAP).

### Behavioural evaluation

Examining how clinicians make antibiotic decisions in both arms of the trial is crucial to (i) identifying the behavioural factors influencing antibiotic prescribing (whether appropriate or not); (ii) quantifying the degree to which the FilmArray test and algorithm influences doctors’ antibiotic decisions, as to assume 100% compliance with its recommendations is neither appropriate nor realistic; and (iii) providing a context for RCT findings. Prescriber behaviour will be a key determinant of the trial outcomes. Rapid molecular diagnostics can only improve antibiotic stewardship if they are appropriately applied. Understanding the drivers of, and barriers to, adoption of rapid molecular-diagnostic-assisted prescribing (e.g. prescriber trust in FilmArray results) will help identify the reasons behind trial success/failure.

Data will be collected using a 1-min questionnaire, developed for INHALE and completed after a specific antibiotic decision. This methodology allows for a range of decisions (e.g. from sites across the UK, out-of-hours decisions) to be consistently captured with minimal disruption to clinical duties. In the intervention arm, the questionnaire explores the decision made after receiving the FilmArray test results. In the control arm, it relates to the empirical antibiotic decision made directly before randomisation. The clinician who made the ultimate decision will be asked to complete the survey: intensivists and specialists working in the ICU will be eligible to participate. To minimise recall bias [34], the clinician will complete the survey as soon as possible after this decision, but no later than 24 h afterwards. The questionnaire asks the clinician to indicate factors influencing their decision-making and rate their agreement with statements about their patient as well as the role of institutional guidelines, the FilmArray test and the algorithm. Survey design was a collaboration between behavioural scientists, intensivists and microbiologists and was informed by a literature review, four focus groups and 35 interviews with ICU prescribers.

We will also conduct semi-structured interviews with clinicians to further explore their perceptions about using molecular diagnostics in practice. Participants will be intensivists and microbiologists who have made antibiotic decisions with the FilmArray during the RCT.

Clinicians will be encouraged to participate via the principal investigator at each site, with interview transcripts anonymised. ICUs are time-pressured environments, and participation rates will be monitored and changes made if the design proves difficult, but the team are experienced, and the proposal is based on feasibility work from earlier work packages. Thematic analysis [35] will be used to identify clinicians’ perceptual and practical barriers and enablers to adopting the FilmArray test and the algorithm. Our findings will aid the development of evidence-based behavioural strategies encouraging molecular diagnostic implementation.

